## Abstract

**Introduction:**

Optimal targets for systemic oxygenation in paediatric critical illness are unknown. Observational data indicate that high levels of arterial oxygenation are associated with poor outcomes in resuscitation of the newborn and in adult critical illness. Within paediatric intensive care units (PICUs), staff prevent severe hypoxia wherever possible, but beyond this there is no consensus. Practice varies widely with age, diagnosis, treating doctor and local or national guidelines followed, though peripheral blood oxygen saturations (SpO_2_) of >95% are often targeted. The overall aim of this pilot study is to determine the feasibility of performing a randomised trial in critically ill children comparing current practice of liberal SpO_2_ targets with a more conservative target.

**Methods and analysis:**

Oxy-PICU is a pragmatic, open, pilot randomised controlled trial in infants and children requiring mechanical ventilation and receiving supplemental oxygen for abnormal gas exchange accepted for emergency admission to one of three participating UK PICUs. The study groups will be either a conservative SpO_2_ target of 88%–92% (inclusive) or a liberal SpO_2_ target of >94%. Infants and children who fulfil all inclusion criteria and none of the exclusion criteria will be randomised 1:1 by a secure web-based system to one of the two groups. Baseline demographics and clinical status will be recorded as well as daily measures of oxygenation and organ support. Discharge outcomes will also be recorded. In addition to observational data, blood and urine samples will be taken to identify biochemical markers of oxidative stress. Outcomes are targeted at assessing study feasibility with a primary outcome of adequate study recruitment (target: 120 participants).

**Ethics and dissemination:**

The trial received Health Research Authority approval on 1 June 2017 (16/SC/0617). Study findings will be disseminated in national and international conferences and peer-reviewed journals.

**Trial registration number:**

NCT03040570.

Strengths and limitations of this studyThis is the first randomised trial to compare conservative and liberal systemic oxygenation targets in mechanically ventilated children.As this is a pilot study, without a formal power calculation, outcomes of clinical significance should be treated as hypothesis-generating only.If deemed to be feasible, the outcomes and evaluation of processes of this study will inform a larger appropriately powered definitive study.The pragmatic design of this study will allow us to assess the ability of clinical staff to adhere to the target treatment groups.

## Introduction

The optimal targets for systemic oxygenation in paediatric critical illness are unknown. Intensive care staff prevent severe hypoxia wherever possible, but beyond this there is no consensus. Practice varies widely with age, diagnosis and treating doctor.^1 2^ This uncertainty about the optimal oxygenation target is illustrated by the variance in national guidelines in even the most common cause of acute infant respiratory distress: respiratory syncytial virus bronchiolitis. The US American Academy of Pediatrics recommends a peripheral blood oxygen saturation (SpO_2_) target >90%, whereas the Scottish Intercollegiate Guidelines Network recommend SpO_2_ >94%.^3^

Oxygenation targets have become a ‘hot topic’ for clinical trials because of observational data suggesting that high levels of arterial oxygenation are associated with poor outcomes in resuscitation of the newborn, adult critical illness, myocardial infarction, postcardiac arrest and possibly also in respiratory failure.^4^ When added to the known risks of severe hypoxia, a ‘U-shaped’ relationship between arterial oxygenation and risk of death emerges.^5 6^ We have recently completed a systematic review of the paediatric literature addressing this issue, and although the data are scarce, the same pattern of increased risk and both high and low levels of arterial oxygenation has been observed.^7^ Our recent cohort study of 7410 critically ill children also demonstrated a ‘U-shaped’ relationship between admission arterial oxygen tension and survival. This pattern persists after adjustment for case-mix (including congenital cyanotic heart disease) and indicators of physiological severity. This complex relationship between oxygenation and outcome may reflect the balance between harm from hypoxia at one end of the oxygenation spectrum (low SpO_2_) and a combination of increased oxygen free radical damage and iatrogenic injury from more aggressive treatments at the other (high SpO_2_).^6^

The lack of evidence indicating the safest oxygen level for a critically ill child needs investigation. Around 19 000 such children are admitted to paediatric intensive care units (PICUs) in the UK annually. Around 75% receive artificial support for ventilation in some form. The primary aim of this artificial ventilation is to support blood oxygen values at a safe level. However, since the optimal level is unknown, clinicians typically default to targeting physiologically normal or even supranormal values. With other variables during critical illness, this approach of ‘normalisation of physiology’ is known to be either harmful or of no benefit.^8–11^ In neonatal and critically ill adult patients, the choice of oxygen targets are known to influence survival rates, lengths of stay and costs. Three large randomised studies in extreme preterm infants compared lower (85%–89%) with higher oxygen targets (91%–95%).^12^ Unexpectedly, an increased risk of death (1.45; 95% CI 1.15 to 1.84; P=0.002) was seen with the lower oxygen targets. In contrast, recent pilot data in adult critical illness demonstrate a trend towards the opposite effect: that is, reduced mortality with lower oxygenation targets in the sickest patients: relative risk 0.49 (95% CI 0.20 to 1.17; P=0.10).^13^ Similarly, harmful effects of supplemental oxygen have been demonstrated in adults with ST elevation myocardial infarction.^14 15^ In October 2016, a single-centre study in adults was stopped early because of a significant survival advantage: absolute risk reduction for intensive care unit mortality (8.6%, 1.7%–15% P=0.01) in the conservative oxygenation group.^16^ Even prior to these data, there has been a move in adult intensive care towards lower oxygen targets, for example, SpO_2_ 88%–95%.^4^

The only paediatric trial data—in non-critically ill children with bronchiolitis—demonstrate equivalent safety of a peripheral oxygen saturation (SpO_2_) target of >90% when compared with >94%. Later hospital discharges were seen with the higher target (ratio of length of stay: 1.28, 95% CI 1.09 to 1.50, P=0.003).^17^

Current practice favours very liberal oxygen targets. We have conducted an analysis of around 7 million SpO_2_ values averaged over 5 s in a single PICU: 30% of recorded values were 100% and >60% were >95%.^18^

### Study aim

The overall aim of this study is to determine if it is feasible to perform a safe, adequately powered and affordable definitive randomised controlled trial in critically ill children comparing current practice of liberal targets for systemic oxygen levels with more conservative targets. The underlying hypothesis of a definitive trial is that the harm of interventions to raise arterial oxygen saturation to >94% exceeds the benefits of these interventions.

### Study objectives

To test the willingness of clinicians to screen, recruit and randomise eligible patients.To estimate the recruitment rate.To test, following randomisation, delivery of and adherence to, the intervention and demonstrate separation between the groups.To test acceptability of the deferred consenting procedures and participant information.To test follow-up for the identified, potential, patient-centred primary and other important secondary outcome measures and for adverse event (AE) reporting.To inform final selection of a patient-centred primary outcome measure.To estimate the characteristics (eg, SD) of the selected patient-centred primary outcome measure to inform sample size estimation.To inform content and time needed for final data collection.To investigate the feasibility of collecting samples suitable for estimation of ischaemic/oxidative injury and antioxidant status.

## Methods and analysis

### Study design and setting

Oxy-PICU is a pragmatic, open, pilot randomised controlled trial in infants and children accepted for emergency admission to participating PICUs. Study recruitment will be at three PICUs and their local PICU transport teams representing typical configurations for UK PICUs (general or combined ICUs in general academic medical centres or within stand-alone children’s hospitals).

### Trial population and eligibility criteria

Infants and children receiving treatment at a participating site who fulfil all of the inclusion criteria and none of the exclusion criteria below:

#### Inclusion criteria

Less than 16 years and more than 38 weeks’ corrected gestational age.Emergency admission accepted to a PICU requiring mechanical ventilation within first 6 hours of face-to-face contact with PICU staff or transport team.Receiving supplemental oxygen for abnormal gas exchange.

#### Exclusion criteria

Death perceived as imminent.Brain pathology/injury as primary reason for admission (eg, traumatic brain injury, post-cardiac arrest, stroke and convulsive status epilepticus without aspiration).Known pulmonary hypertension.Known or suspected sickle cell disease.Known or suspected uncorrected congenital cardiac disease.End-of-life care plan in place with limitation of resuscitation.Receiving long-term mechanical ventilation prior to this admission (non-invasive ventilation (NIV) or invasive ventilation (IV)).Recruited to Oxy-PICU in a previous admission.

### Screening and randomisation

Potentially eligible infants and children will be screened against the inclusion/exclusion criteria by transport team and PICU staff supported by the Oxy-PICU trial team (figure 1). Randomisation will then follow a ‘research without prior consent’ model. Randomisation will occur as soon as eligibility has been confirmed with the aim of commencing treatment as soon as possible within the first 6 hours of the infant or child being in face-to-face contact with the PICU or transport staff. Participants will be randomly allocated (1:1) to either the conservative (88%–92%) or liberal (>94%) oxygen target group by a computer-generated dynamic procedure (minimisation) with a random component. Minimisation will be performed on: age (<12 months/≥12 months), study site and primary reason for admission (lower respiratory tract infection vs other); and degree of abnormality of gas exchange: Saturation/FiO_2_ (S/F) ratio <221 with positive end expiratory pressure >5 versus other. Randomisation will be via a secure web-based system.

**Figure 1 F1:**
[figure not shown]
Trial schema of eligibility, randomisation and study intervention to discharge from PICU. FiO_2_, fraction of inspired oxygen; HFNO, high flow humidified oxygen; IV, invasive ventilation; MAP, mean airway pressure; NIV, non-invasive ventilation; PEEP, positive end expiratory pressure; PICU, paediatric intensive care unit; SpO_2,_ peripheral oxygen saturations.

### Prerandomisation and postrandomisation care

Prior to randomisation, all care will be determined by the clinical team primarily responsible for the child’s treatment and care. Once randomised, all care other than that intended to achieve trial target SpO_2_ will be determined by the clinical team.

### Consent procedures

Patients receiving mechanical support to ventilation requiring supplemental oxygen will most often need oxygen treatment started in a life-threatening emergency, where any delay in commencing treatment will be detrimental. This will make any attempt to obtain fully informed consent from parents/legal representatives during an emergency inappropriate and cause additional anxiety to families who are already distressed by their child’s illness. Consent will therefore follow a deferred consent model following previous work and guidelines in this setting.^19 20^

Once notified of the recruitment of a patient to the study, a delegated member of the site research team will approach the parents/legal representatives as soon as practically and appropriately possible after randomisation to discuss the study and provide a participant information sheet (PIS) (usually within 24–48 hours of randomisation). If the participant has been discharged or has died prior to their parents/legal representatives being approached, then the parents/legal representatives will be approached by an appropriate team member at a later point and will be provided with a standard PIS or a specific PIS for bereaved parents/guardians (B-PIS).

A consent form will be provided including a statement that participation is voluntary and that consent can be withdrawn at any time without consequence (online supplementary material 1). Parents/legal representatives will be allowed time to read the PIS (or B-PIS) and have an opportunity to ask any questions they may have about their child’s participation in Oxy-PICU. Deferred consent can be sought from parents/legal representatives following the death of their child and prior to their departure from the hospital if appropriate.

10.1136/bmjopen-2017-019253.supp1Supplementary file 1

For participants who are discharged alive from PICU but have not been consented prior to discharge from the hospital, a study team member will call their parents/legal representative within five working days of discharge. For all participants discharged prior to consent, their parents/legal representatives will subsequently be sent a covering letter, personalised by the most appropriate clinical team member, and a copy of the relevant PIS and consent form by post 4 weeks after randomisation. If there is no response after 4 weeks of sending the initial letter, a follow-up letter along with the appropriate PIS will be sent to the family. Both letters will explain how to opt-out of the study and provide telephone contact details if parents/legal representatives wish to discuss the study with a member of the site research team. The second letter will provide the same information as the first letter. In addition, this letter will also confirm that if no consent form is received within 4 weeks of receipt of the letter, then the participant’s data (samples collected will be destroyed) will be included in the study unless the family notify the site research team otherwise.^19^

Parents/legal representatives can refuse to give consent (non-consent) or withdraw from Oxy-PICU at any time during the study. All data collected up to the point of withdrawal will be retained and included in the study analysis. In order to monitor non-consent, a minimal dataset will be collected for each parent/legal representative approached but not consented. In the case of non-consent/withdrawal from the study, any samples collected will be destroyed.

### Consent questionnaire

For parents/legal representatives who are approached for consent in person, as part of the PIS, parents/legal representatives will be provided with information about the option to complete a questionnaire regarding their views on the consenting procedures for the Oxy-PICU pilot study (online supplementary material 2). Questionnaires will be used to highlight specific concerns related to the consent procedure or conduct of hospital staff and will be used to inform future research design.

10.1136/bmjopen-2017-019253.supp2Supplementary file 2

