### Outcome measures

As this is a pilot study outcome measures for the study will be focused on assessing the study feasibility for a larger scale definitive study as noted in box below.BoxOutcome measures of the Oxy-PICU feasibility study**Primary outcome measure**Number of eligible patients recruited per site per month.**Secondary outcome measures**Proportion of parents/legal representatives refusing deferred consent.Proportion of eligible patients randomised (target 50%).Distribution of time to randomisation.Proportion of systemic oxygen saturations within the target range in each group.Proportion of patients in each arm requiring other treatments influencing tissue oxygen delivery (blood transfusion and inotropic support).Characteristics and completeness of potential primary endpoints for a definitive study including: length of ventilation, length of paediatric intensive care unit (PICU) stay, PICU mortality and days of organ specific support.Observed adverse events.Time taken for data collection and entry.Distribution of markers of ischaemia and antioxidant status.

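### Acceptability of deferred consent is an objective, but parents' views are sought only where the approach was in person, so the telephone, postal and default-inclusion steps are seen only through refusals and non-consent records

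*Protocol article*

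**What the plan says.** The Study objectives section of the protocol article includes the aim "To test acceptability of the deferred consenting procedures and participant information". It does not restrict this to one route of approach.

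The Consent procedures section then describes several routes:

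- The main route is an approach by the site research team, "usually within 24–48 hours of randomisation".
- For a child who leaves hospital alive before consent, "a study team member will call their parents/legal representative within five working days of discharge".
- All families whose child was discharged before consent are then written to 4 weeks after randomisation, with a second letter if 4 more weeks bring no reply.
- The second letter explains what happens "if no consent form is received within 4 weeks of receipt of the letter": the data are kept in the study unless the family objects, and the samples are destroyed.

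The Consent questionnaire section offers the questionnaire to a narrower group: "For parents/legal representatives who are approached for consent in person". Its stated purpose is modest: "Questionnaires will be used to highlight specific concerns related to the consent procedure or conduct of hospital staff", and to help design later research.

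Two other sources bear on consent, and neither is limited by route. One is the secondary outcome "Proportion of parents/legal representatives refusing deferred consent". The other is a minimal dataset on parents who were approached but did not consent. The Statistical analysis section reports consent data by centre and by arm; route is not named.

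**The concern.** The objective covers the consent procedures as a whole, but the only instrument that asks parents what they thought is confined by rule to one of them. This is an express restriction, not a detail lost in condensing the protocol into an article. The description of the postal pack also lists its contents (covering letter, information sheet, consent form) and names no questionnaire.

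The refusal outcome does not fill the gap. Silence after two letters may mean agreement, distress, or a letter that never arrived. A count of refusals cannot separate these, because a silent family is simply kept in.

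At stake is what the pilot may conclude. It is meant to show whether the consent model works for a definitive trial. As written, it could report the model as acceptable without having asked any parent about being telephoned, written to, or included by default.

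**Working it through.** **Scale.** The article expects about 120 children in 6 months from three units at 4 to 10 per month. Read as a rate per site, this gives 3 × 6 × 4 = 72 to 3 × 6 × 10 = 180, and 120 needs 120 / 18 = 6.67 per site per month, which lies inside the stated range. I use 120 only as a scale; the point does not depend on it.

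**Step 1: coverage of each consent step.**

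| Step | Approximate timing | Views sought? | Other record |
|---|---|---|---|
| In-person approach | usually 24–48 hours after randomisation | yes, optional | refusal, non-consent dataset |
| Telephone call | within 5 working days of discharge | no | refusal, non-consent dataset |
| First letter | week 4 | no | opt-out, non-consent dataset |
| Second letter | week 8 (4 + 4) | no | opt-out, non-consent dataset |
| Inclusion by default | about week 12 (4 + 4 + 4) | no | not a refusal |

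A family met in person who later moves to the postal route may have had the questionnaire, but before any letter. Its answers need not reflect the later steps.

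**Step 2: what the questionnaire could miss.** Let f be the share of families not offered it, and A the proportion finding consent acceptable. Then

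A(all) = (1 − f) × A(in person) + f × A(remote)

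bias = A(in person) − A(all) = f × [A(in person) − A(remote)]

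The documents give neither f nor either value of A. Assume f from 5% to 40%, and a difference from −10 to +40 percentage points:

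| f | Families of 120 | Difference −10 | 0 | +10 | +20 | +40 |
|---|---|---|---|---|---|---|
| 5% | 6 | −0.5 | 0 | 0.5 | 1.0 | 2.0 |
| 20% | 24 | −2.0 | 0 | 2.0 | 4.0 | 8.0 |
| 40% | 48 | −4.0 | 0 | 4.0 | 8.0 | 16.0 |

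Entries are percentage points; a positive sign means acceptability looks too high. Over these assumptions the bias runs from −4 to +16 points, and it is zero if remote families feel as others do.

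**Step 3: what the refusal proportion could miss.** Assume 10% of families who answer refuse, and let s be the share who never answer. With silent families in the denominator, the proportion is 10% × (1 − s):

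- s = 5%: 9.5%
- s = 10%: 9.0%
- s = 20%: 8.0%
- s = 30%: 7.0%

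The more families stay silent, the lower the refusal figure, whatever they think. At s = 20%, the share who object could be anything from 8.0% (no silent family objects) to 8.0% + 20% = 28.0% (all do). The refusal figure alone cannot say where in that range the truth lies.

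**The case against.** The strongest reply is that the remote steps are observed. Both letters explain how to opt out and give a telephone contact, the refusal outcome counts refusals by any route, and the non-consent dataset and consent reporting are not restricted either. This stands. A reader might infer that the remote route is never evaluated, and the documents do not support that. What is missing is narrower: parents' views on it.

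A second reply is that the questionnaire is an optional tool for finding concerns, with no stated percentage or threshold that could be biased. This also stands, and it makes the figures in Step 2 an illustration of what would follow if answers were summarised as a rate. It does not close the gap, since concerns specific to calls, letters or default inclusion are the ones it cannot surface.

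A third reply is that the remote route is a fallback. The call is triggered by leaving hospital, not intensive care, without consent, so a short intensive care stay does not by itself prevent a meeting in person. Parents of a child who has died may be approached before they leave. The affected group may therefore be small, and its size is not given.

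Finally, the full protocol and the supplementary questionnaire are not shown. The questionnaire is introduced through the information sheet, and an information sheet is also posted. But the opening condition of the Consent questionnaire section restricts the offer to approaches in person, and nothing in the article lifts that restriction.

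**Conclusion.** The point holds in a limited form. An objective stated without restriction by route is served by a views questionnaire restricted to one route, so part of the objective goes unanswered. The remote and default steps are visible only through refusals, opt-outs and non-consent records, and silence is not a refusal.

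A reader might go further and infer that acceptability will look too good. That requires remote families to be less accepting, or silent families to be objectors, and the documents establish neither. Nor do they say that the definitive trial would rely heavily on the postal route. The supportable statement is that acceptability may be overstated, with size and direction unknown. The ranges of 6 to 48 families and −4 to +16 points rest wholly on the assumed shares and differences.

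The change is worth making because it is cheap and bears on a stated objective. It does not call the rest of the pilot into question.

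**What to change.** 1. Amend the Consent questionnaire section so that the optional questionnaire is also enclosed with the first postal pack, already sent 4 weeks after randomisation. For bereaved families, leave enclosure to the discretion of the clinical team member who personalises the letter.
2. Report consent status over all randomised children in three categories: consented; refused or withdrawn; no response and included by default. Split this by route (in person, or telephone and post). It should need little beyond records the sites already keep, plus a note of the route.
3. If the questionnaire is not extended, state that the acceptability conclusion applies to in-person deferred consent only.

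The cost is one sheet in a letter already being posted and a minor ethics amendment. Postal response will probably be low, so the number sent and returned must stand beside the results. One limit remains: the article places the default-inclusion notice in the second letter, so a sheet in the first pack gathers views on the call and the letter, and the default step would be seen mainly through the no-response category.
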